### Ethics

The study follows the guidelines of the Declaration Helsinki and existing guidelines in Spain and the European Union for the protection of patients in clinical trials. As noted, all participants will be volunteers, and they will sign the online informed consent to form part of the study once it has been explained to them. Participants will have the possibility of withdrawing from the study at any time. The recruitment of participants will be carried out by qualified personnel from a clinical point of view. Participants allocated to the *WL* condition will be offered the opportunity to receive the *TIBP* or the *TIBP + PA* intervention after the waiting time has ended. Based on the literature, no special difficulties are expected. However, any undesired event would not only mean the participant’s departure from the trial, but s/he would also be offered the possibility of receiving psychological care at the Emotional Disorder Clinic in Universitat Jaume I, or of being referred if his/her medical condition required it.

A fundamental aspect in a project of this nature is data protection. To protect information, strategies using personal passwords and data via AES encryption (AES-256; Advanced Encryption Standard) will be used. Personal data will be replaced by codes and data, which must be collected by clinicians (e.g. age, sex, address, and phone), stored separately from other data, and only made available to researchers responsible for the study, always protecting the right to privacy.

The study has been approved by the Ethics Committee of Universitat Jaume I (Castellón, Spain). The trial was registered at clinicalstrial.gov as NCT02578758.

### Interventions

We have developed a manualized protocol, based on the transdiagnostic perspective for the treatment of ED: MDD, DD, OCD, PD, AG, GAD, SAD, ADNOS and MDNOS. The treatment protocol is structured in a patient handbook and a therapist handbook ([name], [name], [name], [name]. A Transdiagnostic Treatment for Emotion Disorders: Manualized Treatment Protocol, unpublished). The modules in each intervention protocol are described briefly in the following section.

We have adapted this protocol from classic perspectives derived from the UP [9, 17] and some strategies from Marsha Linehan’s protocol [66]. The protocol includes the following core components mainly addressed to down-regulate NA: present-focused emotional awareness and acceptance, cognitive flexibility, behavioral and emotional avoidance patterns, and interoceptive and situational exposure. The protocol also includes traditional therapeutic components of evidence-based treatment for ED (Psychoeducation, Motivation for change, and Relapse prevention). In addition, in order to promote psychological strengths and enhance well-being [67], we have included a PA-regulation component based on behavioral activation strategies [68], strategies to promote pleasant and significant activities linked to values and life goals, and strategies to enhance personal strengths, positive feelings, positive cognitions, and positive behavior [67, 69]. This component also includes the Well-being Therapy (WBT) [70, 71] strategy of identifying examples of well-being and negative cognitions (“interrupting thoughts”) that interfere with these moments of well-being, in order to modify these interfering cognitions. Some notions of Fredickson’s Broaden-and-Build Theory are also included to explain the mechanisms behind positive emotions [31].

#### Transdiagnostic Internet-based protocol (TIBP)

This intervention protocol consists of twelve more traditional modules mainly designed to down-regulate NA. Each module has specific objectives:
*M1. Emotional disorders and emotion regulation.* The purpose of this module is to provide information about the central role of emotion regulation in emotional disorders. Brief descriptions of the program modules, as well as videos with examples of people suffering from different ED, are also presented.
*M2. Motivation for change.* The objective of this module is to enhance motivation for change by recognizing that attitudes towards change can be ambivalent and that motivation fluctuates. The main objective is to analyze the advantages and disadvantages of changing, emphasize the importance of being motivated, and highlight the importance of establishing significant life goals.
*M3. Understanding the role of emotions.* This module provides information about the adaptive roles and functions of emotions. It also shows the three-component model of emotions.
*M4. The acceptance of emotional experiences.* This module focuses on the awareness and role of acceptance of emotional experiences, as well as their importance in the treatment.
*M5. Practicing acceptance.* The objective of this module is to continue to learn about the acceptance of emotional experiences and increase awareness of physical sensations, thoughts, emotions, and daily activities.
*M6. Learning to be flexible.* This module teaches participants to be more cognitively flexible in order to see life situations from different perspectives, showing the importance of maladaptive ways of thinking and learning how to identify them in the maintenance of emotional disorders.
*M7. Practicing cognitive flexibility.* This module aims to teach the patients how to modify maladaptive ways of thinking. It also provides information about intrusive thoughts and how to deal with them.
*M8. Emotional avoidance.* The aim is to teach the patients emotion avoidance strategies that contribute to the maintenance of emotional disorders.
*M9. Emotion Driven Behaviors (EDBs).* The aim is for patients to learn the concept of EDBs and replace their own maladaptive EDBs with other more adaptive behaviors.
*M10. Accepting and facing physical sensations.* The objectives are to teach the patients the role of physical sensations in their emotional response and train them in interoceptive exposure, in order to increase tolerance and promote habituation to physical sensations.
*M11. Facing emotions in the contexts where they occur.* This module aims to increase tolerance to emotions and reduce avoidance behavior. The purpose is to construct exposure hierarchies to help patients to begin to face the avoided situations that contribute to the maintenance of the problem.

#### Transdiagnostic Internet-based protocol + positive affect component (TIBP + PA)

This intervention protocol is made up of 16 therapeutic modules. The first 12 modules have been described above in the first condition *- (TIBP) -* and the other 4 are aimed to up-regulate PA by understanding and capturing positive emotions, and training adaptive positive emotion regulation strategies. These four modules are described as follows:
*M12. Learning to move on.* This module focuses on the role of behavioral activation. The aim is to teach the importance of ‘moving on’ in acquiring a proper level of activity and involvement in life. It motivates the patient to get involved in meaningful activities and become engaged in his/her life.
*M13. Learning to enjoy.* This module helps the patient to see the importance of positive emotions and teaches procedures that generate positive experiences, promoting involvement in pleasant and significant activities and contact with others. This module involves enjoying positive experiences and “savoring” positive aspects of life in order to enhance wellbeing.
*M14. Learning to live.* This module takes a further step in enhancing PA, understanding the importance of identifying the individual’s own psychological strengths, and selecting and carrying out meaningful activities linked to values and goals in life. This module provides strategies to achieve psychological well-being and resilience. The aim is to improve the individual’ abilities and live a life full of purpose and meaning.
*M15. Living and learning.* This module focuses on developing an action plan to boost the individual’s psychological strengths. It focuses on the importance of developing and enhancing one’s own strengths and starting to work for life and the future.
*M16. Relapse prevention (this module is the same for both conditions: (TIBP) and (TIBP + PA).* It aims to strengthen the strategies learned throughout the program, schedule future practice, and teach how to identify and cope with future high- risk situations.

### Adaptation to the web

This protocol has been adapted to a multimedia web platform (video, images, etc.) and can be applied over the Internet (https://www.psicologiaytecnologia.com/). It is developed for optimal use on a PC or a tablet, and it allows individuals to do the modules from their home and at their own pace. The ease of use of the program has been strengthened because it presents a streamlined navigation, which allows users with less experience in handling new technologies to know where they are and how to keep moving forward at any time. The web adaptation of the protocol is the same in both conditions (TIBP and TIBP + PA), with the only difference being the inclusion or not of the modules that contain the PA-regulation component.

Duration of the program can vary among users, and participants in both treatment conditions have access to the protocol for a maximum period of 18 weeks. The program recommends working on one module for at least one entire week, and it sends messages encouraging the patient to continue to work to benefit from it. In both conditions, the modules include exercises and tasks to practice each technique and skill. Moreover, the platform is ready to welcome all participants with information about the treatment and its objectives, as well as general information and recommendations about how to benefit from it.

Regarding the assessment of patients within the program, after the “Welcome”, initial online questionnaires are presented as the pre-treatment assessment. In addition, post-module brief questionnaires to evaluate anxiety, depression, and positive/negative affect (OASIS, ODSIS, PANAS) are also filled out throughout the program. A noteworthy aspect of the program is that it allows the therapist to have access to all this information and receive an alert if the patient’s condition worsens. The program includes suicide risk alarms that consist of an email to the clinical team with information about a high risk of suicide. These alarms are generated when the system detects that the participant rated high on the suicidal ideation items. It allows the clinician to contact the patient and evaluate the actions that should be taken to protect him/her. Finally, after the treatment, the participants complete the online assessment in the post- and follow-up periods.

All the modules are sequential, which allows the participant to move through the program step by step. The web platform was designed to optimize the understanding of the modules’ content. It has different multimedia elements (vignettes, videos, audios,...) that help the user to assimilate the different psychological techniques in the easiest way. The modules always follow the same structure: they start with questions related to the previous module, continue with the specific contents of the module, then propose the exercises, and finally present a series of simple self-assessment questions designed to verify whether the content presented has been understood correctly. In addition, at the end of each module, homework tasks are indicated to work on what was presented in the module. Performing these tasks helps to consolidate everything learned in the program. Participants have the opportunity to obtain printable documents (PDF) with summaries of each module.

The web platform has four complementary tools that appear on the main menu of the protocol: 1) “Home”, which is the starting point from which the participant can access the other sections of the protocol; 2) “Calendar”, which is a tool that allows the participant to know about pending or achieved tasks as well as his/her current point in the program; 3) “Review”, which allows the participant to review the treatment modules already completed; and 4) “How am I?”, which allows participants to monitor their progress through a set of graphs. It is a tool that provides feedback to participants about their evolution during the program with regard to their emotional distress (anxiety and sadness) and their positive and negative affectivity.

### Support

In each of the two treatment conditions, we will provide human support and ICT support to all participants.

Human support will be provided by weekly phone calls (maximum of 5 min) during the treatment period in order to resolve any difficulties or doubts about the use of the online protocol, or to remind them of the importance of doing the homework tasks and reviewing the treatment contents. During these weekly phone calls, we will also encourage participants to continue to use the protocol, and reinforce them for engaging in the treatment. At the end of the treatment period, participants will be reminded that they will be contacted again for follow-up assessments.

ICT support will consist of two weekly mobile phone text messages reminding participants of the importance of reviewing the modules and encouraging them to do the homework tasks. Some examples of these text messages are: “Hi there! Don’t hesitate to review the modules you’ve already completed if necessary. Remember, practice makes perfect!”or “Hi there! Don’t give up on your module tasks! Dedicate some time and effort to them. Remember, it’s ideal to complete one module each week”. These messages will be randomized, so that participants do not always receive the same content. A professional platform will be used to send these messages (www.trendoo.es). The online treatment also contains several multiple-choice questions about the contents seen in each module. The program immediately provides the participant with the correct feedback and a simple explanation. This aspect is repeated throughout all the treatment modules. In addition, the ICT support includes automatic e-mails with reminders to access the program when participants have not entered in the past 15 days.

### Measures

#### Diagnostic interview

*Mini International Neuropsychiatric Interview Version 5.0.0* (MINI) [72]. It is a short, structured, diagnostic psychiatric interview for DSM-IV and ICD-10 diagnoses. The MINI can be used by clinicians after a brief training session. Nonclinical interviewers should receive more intensive training. This interview has excellent inter-rater reliability (k = .88–1.00) and adequate concurrent validity with the Composite International Diagnostic Interview [73]. The MINI has been translated and validated in Spanish [74].

#### Primary outcomes measures

##### *Beck Depression Inventory (BDI-II)* [75]

It is one of the most widely-used questionnaires in the evaluation of depression severity. The BDI consists of 21 items, scored on a scale from 0 to 3, covering all the different symptoms of major depression disorder. The total score on this questionnaire can yield a maximum of 63 points. The instrument has shown good internal consistency (α = 0.76 to 0.95). The Spanish version of this instrument has also shown high internal consistency (α = 0.87) for both general and clinical populations (α = .89) [76].

##### *Beck Anxiety Inventory (BAI)* [77]

The BAI is a 21-item symptom checklist designed to assess anxiety symptoms. Each item is scored on a 0 to 3 point severity scale, and the total scores range between 0 and 63. The internal consistency of the BAI has been found to range from .85 to .94. The Spanish version of the BAI has shown high internal consistency (α = .93) [78].

##### *Positive and Negative Affect Scale (PANAS)* [79]

The PANAS consists of 20 items with a range from 1 (very slightly or not at all) to 5 (extremely). Respondents have to indicate the extent to which they experienced the feeling or emotion during the past few weeks. This scale evaluates two independent dimensions: PA and NA. The maximum score for each subscale is 50. The scale showed excellent internal consistency (α between .84 and .90) and convergent and discriminant validity. The Spanish version has demonstrated high internal consistency (α = 0.89 and 0.91 for PA and NA in women, respectively, and α = 0.87 and 0.89 for PA and NA in men, respectively) in college students [80].

### Secondary outcomes measures

#### Diagnosis-specific measures

Depending on each participant’s main diagnosis, different instruments will be implemented.OCD: Obsessive-Compulsive Inventory-Revised (OCI-R) [81]. The OCI-R is a short scale made up of 18 items rated from 1 to 4 to assess obsessive-compulsive symptoms. The OCI-R yields six subscales: washing, checking, ordering, obsessing, hoarding, and neutralizing. The OCI-R has good internal consistency (α = .81 to .93), good to excellent test-retest reliability (α = .57 to .91), good convergent validity, and a solid factor structure. The Spanish version of the OCI-R has been found to be good (α = .86) [82].PD/AG: Self-Reported Panic Disorder Severity Scale (PDSS-SR) [83]. The PDSS-SR is a 7-item self-report measure of panic disorder severity. This scale assesses panic attack frequency, distress during panic attacks, severity of anticipatory anxiety, fear and avoidance of agoraphobic situations, fear and avoidance of physical sensations, and work and social impairment. The scale has shown excellent reliability (α = .917), test-retest reliability (ICC = .81), and sensitivity to change. The psychometric analysis of the Spanish version showed excellent internal consistency (α = .85), good test-retest reliability, and adequate convergent validity [82].GAD: Penn State Worry Questionnaire (PSWQ) [84]. It is a questionnaire that evaluates symptoms related to GAD. The PSWQ is a 16-item self-report questionnaire that assesses the tendency to worry, as well as the intensity of the worry characteristic of GAD as an uncontrollable, generalized, and excessive experience. The PSWQ has demonstrated good internal consistency ranging from .91 to .95, and good validity and test-retest reliability. The Spanish version of the scale showed an internal consistency of .90 and a test-retest reliability of .82, as well as adequate convergent and discriminant validity [85].SAD: Social Interaction Anxiety Scale (SIAS) [86]. This scale is a 20-item self-report measure rated on a 5-point scale ranging from 0 (*not at all characteristic or true of me*) to 4 (*extremely characteristic of me*). It assesses cognitive, affective, and behavioral reactions in interactive social situations (symptoms related to social phobia). The SIAS has high internal consistency (α = .88 to .94) and good test-retest and discriminant reliability, as well as adequate construct validity. The Spanish validation of the scale showed adequate internal consistency [87].

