### Sample size

To determine the sample size, the effect sizes found in the literature have been considered. An RCT using the UP in a traditional face-to-face approach [33] obtained effect sizes of 0.56 for anxiety, measured with the BAI, and 1.11 for depression, measured with BDI-II. The mean effect size indicated in a recent meta-analysis [39] comparing transdiagnostic computerized cognitive-behavior therapy (CBT) to waitlist control was g = .93 for anxiety and g = .88 for depression.

Adopting a more conservative approach than those of the aforementioned studies, we assumed an effect size of 0.5 (Hedges’ g), which, following Cohen [62], can be considered an effect size of medium magnitude. As our design included three experimental conditions (*TIBP*, *TIBP + PA*, *WL*), a between-groups one-way ANOVA was assumed for the statistical analyses. Therefore, calculations of the necessary sample size cannot be based on Hedges’ *g* index for effect size, but rather on the *f* index [62]. Following Cohen [62], *f* = 0.25 represents an effect size of medium magnitude (and equivalent to *g* = 0.5). Thus, considering an alpha of .05 and a statistical power of .80, the total sample size required to warrant these conditions contains 159 participants (53 participants per group). To control the maximum possible loss of subjects during treatment, based on the literature about Internet-based treatments, a 30% dropout rate is expected [53, 63]. Thus, the required sample size should have 207 participants in all (69 participants per group). These calculations were accomplished with the software program *G*Power 3.1* [64].

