### Data analyses

Intention-to -treat analyses and per protocol analyses will be performed, and CONSORT recommendations will be followed [98]. First, the three groups will be compared to verify that there are no significant differences among them at baseline on the outcome measures in order to confirm that they are comparable after randomization. One-way ANOVAs for continuous variables and Chi-squared tests of independence for categorical ones will be used. For the continuous outcome measures on the posttest, the homoscedasticity assumption will be assessed with the Levene test. Where this assumption is met, the usual *F*-test will be applied to compare the posttest means for the three experimental conditions. If the homoscedasticity assumption is not met, the Brown-Forsythe *F*-test will be applied. Statistically significant *F*-tests will be followed by post hoc comparisons. In particular, the Tukey procedure will be applied where the homoscedasticity assumption is met, and the Games-Howell procedure if this assumption is not met.

The intention-to-treat principle will be used when analyzing primary and secondary post-treatment data and data collected at the 3- and 12-month follow-ups, using mixed-effect models with full information maximum likelihood estimation. This method has been recommended due to its flexibility on repeated-measures ANOVAs in handling missing data more appropriately [99]. To complement the results of the ANOVAs and post hoc comparisons, effect sizes will be calculated by using the standardized mean difference proposed by Cohen [62]. These effect sizes will be calculated to assess both within- and between-group changes, all of them based on a pooled standard deviation.

Although per protocol analyses (completers only analysis) suffer from selection bias, they will also be conducted to help to draw conclusions about the maximum treatment efficacy in patients who comply fully with the treatment [100].

When the trial ends, the analytic methodology for the RCT will be reviewed before analyzing the data in order to select the most appropriate analytic procedures.

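### Full maximum likelihood is named for the diagnosis-specific scales too, where small subsets would make its standard errors too small and raise a nominal 5% test to about 6–10%

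*Protocol article*

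**What the plan says.** The Diagnosis-specific measures section assigns the secondary symptom scales by principal disorder: "main diagnosis, different instruments will be implemented". The OCI-R is for OCD, the PDSS-SR for panic disorder and agoraphobia together, the PSWQ for GAD and the SIAS for social anxiety disorder. The Interventions section lists nine eligible diagnoses: the treatment is "based on the transdiagnostic perspective for the treatment of ED: MDD, DD, OCD, PD, AG, GAD, SAD, ADNOS and MDNOS". Five of the nine (OCD, PD, AG, GAD, SAD) are served by one of the four scales.

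The Data analyses section has two strands. Post-test means are compared by an F-test (Brown-Forsythe if variances differ), followed by Tukey or Games-Howell comparisons. The intention-to-treat analysis of primary and secondary outcomes, at post-treatment and both follow-ups, is done "using mixed-effect models with full information maximum likelihood estimation". No exception is made for scales collected in a subset. No covariance structure, reference distribution or degrees-of-freedom method is given. The section ends by saying that the methods will be reviewed before the data are analysed.

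**The concern.** Maximum likelihood estimates the variance as if the fixed effects were known. With three arms and four assessment times, a model with a separate mean for each arm and time fits 12 means. With 207 participants this matters little. With a few dozen or fewer, the variance estimate is noticeably too low, confidence intervals are too narrow and the false-positive rate exceeds its nominal level. An apparent gain on obsessive-compulsive, worry, social-anxiety or panic symptoms could then be partly an artefact of the estimator, in the subsets where a chance result is most easily read as a disorder-specific benefit.

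**Working it through.** **The plan's own figure.** The Sample size section assumes a three-group one-way ANOVA with f = 0.25, "considering an alpha of .05 and a statistical power of .80". With noncentrality N·f² and 2 and N − 3 degrees of freedom, power is 0.797 at N = 156 and 0.805 at N = 159, so 159 (53 per arm) is reproduced. Then 53 × 1.3 = 68.9, rounded to 69, and 3 × 69 = 207. So 207 is the number randomised.

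**Subset sizes (assumption: equal split over nine diagnoses; the article gives no counts).**
- OCI-R, PSWQ and SIAS: 207/9 = 23 each, 7.7 per arm. With the 30% loss that the plan expects, 23 × 0.7 ≈ 16.
- PDSS-SR (PD plus AG): 2 × 23 = 46, 15 per arm. After 30% loss, 46 × 0.7 ≈ 32.
- Upper bound for any diagnosis mix: each participant has one main diagnosis, so four scales share at most 207 people. Even with no mood or NOS diagnoses, 207/4 = 51.75, so the smallest subset cannot exceed 51. After 30% loss, 51 × 0.7 ≈ 36.

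**Exact error rate, complete data, a separate mean for each arm and time.** For a between-arm contrast in change from baseline, the ML variance is (n − 3)/n times the unbiased one. The true type I error is therefore:
- z reference: P(|t with n − 3 df| > 1.96·√((n − 3)/n))
- three-arm test against chi-square with 2 df: P(F(2, n − 3) > (5.99/2)·(n − 3)/n)

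At n = 23, √(20/23) = 0.933 and 1.96 × 0.933 = 1.828. The two-sided tail of t with 20 df beyond 1.828 is 8.3%.

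| n | SE ratio, ML to unbiased | ML, z | ML, t | ML, chi-square (2 df) |
|---|---|---|---|---|
| 16 | 0.901 | 10.1% | 7.3% | 12.7% |
| 23 | 0.933 | 8.3% | 6.6% | 9.9% |
| 32 | 0.952 | 7.2% | 6.1% | 8.3% |
| 36 | 0.957 | 7.0% | 6.0% | 7.9% |
| 46 | 0.967 | 6.5% | 5.8% | 7.2% |
| 51 | 0.970 | 6.3% | 5.7% | 7.0% |
| 207 | 0.993 | 5.3% | 5.2% | 5.5% |

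**Simulation.** Random-intercept model, arm-by-time means, 2 or 4 visits, between-visit correlation 0.3 or 0.6, loss 0 or 30%, about 6,000 runs per setting, no true effect:
- 8 per arm, ML: z 6.9–9.6%, chi-square 8.1–12.7%, t 6.3–7.7%.
- 15 per arm, ML: z 5.9–7.6%, chi-square 6.1–8.3%.
- 8 per arm, REML with a large-sample reference: z 5.0–7.1%, chi-square 5.3–9.0%.
- 8 per arm, REML with a t reference (within-subject df): 4.7–5.8%.

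Changing the estimator alone therefore does not restore 5%, and neither does changing the reference alone.

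**The case against.** The case on the other side is substantial, and most of it limits the point without removing it.

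- *No count per diagnosis is stated.* Correct. Stratified randomisation balances diagnoses across arms; it does not make them equally common. A reader might take 23 people, 8 per arm, as a figure of the plan that applies to all four scales. It is an assumption, and even under it the PDSS-SR has about 46. Only the upper bound of 51 for the smallest subset holds whatever the mix.
- *The reference distribution is not stated.* Correct. Part of the inflation comes from a large-sample reference, a detail that may sit in an analysis plan not shown. With a t reference, ML at 8 per arm still gives about 6–8%.
- *A rate of 11% at 8 per arm.* A simulation with an unstructured covariance, Wald tests against 1.96 and 30% loss gave 11.0%. A reader might quote that as what the plan implies, but the article names neither that covariance nor that test.
- *Every diagnosis-specific result is affected.* The article does not support this. The post-test F-tests with Tukey or Games-Howell use unbiased variance estimates. The intention-to-treat and follow-up analyses, however, are assigned to the mixed models.
- *The choice is not final.* The review of methods before analysis leaves room to change it, so the estimator is named but not irrevocably fixed. The review clause does not withdraw maximum likelihood, and offers no alternative.
- *The method was chosen for missing data.* True, but restricted maximum likelihood uses the same available observations under the same missing-at-random assumption.
- *Little depends on it.* None of the stated hypotheses names a diagnosis-specific scale. This bears on the weight of the point, not on whether it is right.

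**Conclusion.** The point holds in limited form. The article names full maximum likelihood for scales that will be analysed in small subsets, and the bias there is real. Assuming an equal split over nine diagnoses, and that each scale is modelled in its own subset with arm-by-time means, the mixed-model tests run at about 7–10% (z) or 6–8% (t) at 8 per arm, and at about 6–8% at 15 per arm. The upper extreme, about 13%, needs the three-arm chi-square test at 8 per arm with 30% loss. Even at the most favourable diagnosis mix, the smallest subset would run at 6.3% (z) before loss and 7.0% after it. On 207 participants the rate is 5.3%, so the primary outcomes are practically unaffected. This is minor to moderate, and confined to the mixed-model results for secondary outcomes.

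**What to change.** In the Data analyses section, or at the methods review it already foresees, replace full maximum likelihood by restricted maximum likelihood with Kenward-Roger or Satterthwaite degrees of freedom, for all outcomes. Both parts are needed, because restricted maximum likelihood with a large-sample reference still gives about 5–9% at 8 per arm. The change takes one sentence, keeps the stated missing-data rationale and leaves the primary results practically as they are. Its cost is somewhat wider intervals on the diagnosis-specific scales. The change should be recorded before outcome data are examined. It would also help to report the number analysed per arm for each diagnosis-specific scale, so that readers can see how small the subsets are.
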